#### **Grouping:**

Study group is the co-purified DTaP group: The target number of enrollment is 240. Blood samples will be collected before immunization on D0 and the subjects will then be vaccinated with the co-purified DTaP (0.5 mL/vaccine); blood samples will be collected on D28.

Control group is the DT group: The target number of enrollment is 240. Blood samples will be collected before immunization on D0 and the subjects will then be vaccinated with the DT (0.5 mL/vaccine); blood samples will be collected on D28.

### **3.2 Blood Collection**

Two blood samples are collected from each subject for serum antibody testing.

**Pre-immunization blood collection:** A total of 3.0 mL of venous blood will be collected from all subjects before immunization. The isolated serum samples will be aliquoted into 2 tubes (with at least 0.6 mL serum/tube) and stored at -20°C or below.

**Post-immunization blood collection:** A total of 3.0 mL of venous blood will be collected on D28 after the second dose. The isolated serum samples will be aliquoted into 2 tubes (with at least 0.6 mL serum/tube) and stored at -20°C or below. The time window for blood collection is +14 d.

### **3.3 Immunogenicity Assessment**

Concentrations of antibodies against pertussis, diphtheria, and tetanus were measured by the Enzyme-Linked Immunosorbent Assay (ELISA) method.

#### **Immunogenicity assessment criteria for pertussis vaccine:**

Positive: Antibody titer is  $\geq 0.1$  IU/mL.

Seroconversion: Antibody concentration is  $< 0.1$  IU/mL before immunization and  $\geq 0.1$  IU/mL after immunization; or antibody concentration is  $\geq 0.1$  IU/mL before immunization and is increased  $\geq 4$ -fold after immunization.

Antibody level: Geometric mean concentrations (GMCs) of serum antibody before and after pertussis vaccine immunization as well geometric mean increase (GMI) in serum antibody after immunization.

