## Supplementary information

| Contents                                                                                                                                                                                | Page |
|------------------------------------------------------------------------------------------------------------------------------------------------------------------------------------------------|-------------|
| Supplementary Table 1. Seroconversion rates to co-purified DTaP or DT before and day 28 after vaccination based on subgroups that were positive or negative for antibodies at baseline. | 2           |
| Protocol                                                                                                                                                                                | 3-18        |
| CONSORT 2010 checklist                                                                                                                                                                  | 19-20       |

**Supplementary Table 1.** Seroconversion rates to co-purified DTaP or DT before and day 28 after vaccination based on subgroups that were positive or negative for antibodies at baseline.

| Baseline antibody | co-purified DTaP |              | DT  |              | P |
|-------------------|------------------|--------------|-----|--------------|----------|
|                   | N                | Rate, n (%)  | N   | Rate, n (%)  |          |
| anti-PT    |                  |              |     |              |          |
| ≥20 IU/ml         | 21               | 11(52.38)    | 8   | 0(0)         |          |
| < 20 IU/ml        | 213              | 179 (84.04)  | 216 | 5 (2.31)     |          |
| anti-FHA   |                  |              |     |              |          |
| ≥20 IU/ml         | 85               | 31 (36.47)   | 69  | 0(0)         |          |
| < 20 IU/ml        | 149              | 143 (95.97)  | 155 | 8 (5.16)     |          |
| anti-DT    |                  |              |     |              |          |
| ≥0.1 IU/ml        | 87               | 87 (100.00)  | 77  | 77 (100.00)  | 1.000    |
| < 0.1 IU/ml       | 147              | 147 (100.00) | 147 | 147 (100.00) | 1.000    |
| anti-TT    |                  |              |     |              |          |
| ≥0.1 IU/ml        | 214              | 207 (96.73)  | 203 | 174 (85.71)  | <0.001   |

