|                   | 
enrollment is 240. Blood samples will be collected before immunization on D0 and the subjects will then be vaccinated with the co-purified DTaP (0.5 mL/vaccine); blood samples will be collected on D28.
 
Control group is the DT group: The target number of enrollment is 240. Blood samples will be collected before immunization on D0 and the subjects will then be vaccinated with the DT (0.5 mL/vaccine); blood samples will be collected on D28.
                                                                                                                                                        |
| Hypotheses | 
1.The seroconversion rate of pertussis antibody in 6-year-old children vaccinated with co-purified DTaP vaccine is not less than 70%.
 
2. There was no significant difference in the seroconversion rates of diphtheria and tetanus antibodies between 6-year-old children vaccinated with co-purified DTaP vaccine and DT.
                                                                                                                                                                                                                                                                                       |
| Vaccines   | 
Vaccine 1: co-purified DTaP
 
Manufacturer: Chengdu Institute of Biological Products Co., Ltd.
 
Strength: 0.5 mL/vial/dose, the titer of acellular pertussis vaccine, diphtheria vaccine and tetanus vaccine shall not be lower than 4.0 IU, 30 IU and 40 IU respectively.
 
Vaccine lot no.: 20220311
 
Vaccine 2: DT
 
Manufacturer: Wuhan Institute of Biological Products Co., Ltd.
 
Strength: 0.5 mL/vial/dose, the titer of diphtheria toxoid is not less than 30IU; the titer of tetanus toxoid should not be lower than 40IU.
 
Vaccine lot no.: 202112020-2
 |

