## 1. STUDY OBJECTIVE

### 1.1. Primary objective

The primary outcomes of the study were the seroconversion rates and seropositive rates of anti-pertussis antibodies in the co-purified DTaP group, as well as a comparison of seroconversion rates and seropositive rates of anti-diphtheria and anti-tetanus antibodies in the co-purified DTaP and DT groups.

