#### **Immunogenicity assessment criteria for diphtheria vaccine or tetanus vaccine:**

Positive: Antibody titer is  $\geq 20$  IU/mL.

Seroconversion: Antibody concentration is  $< 20$  IU/mL before immunization and  $\geq 20$  IU/mL after immunization; or antibody concentration is  $\geq 20$  IU/mL before immunization and is increased  $\geq 4$ -fold after immunization.

Antibody level: Geometric mean concentrations (GMCs) of serum antibody before and after pertussis vaccine immunization as well geometric mean increase (GMI) in serum antibody

after immunization.

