### 3.7 Sample Size Estimation

The sample size was estimated using an objective performance criteria method. Assuming the target value was 70% of the seroconversion rate of anti-pertussis in the co-purified DTaP group after vaccination, with a two-sided  $\alpha$  of 0.05, a power of 90%, and a potential loss to follow-up of 15%, we estimated at least a sample size of 240 participants per group.

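### The antibody cut-offs in Section 3.3 are reversed relative to Supplementary Table 1, so no primary endpoint has one agreed definition

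*Combined protocol and SAP*

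**What the plan says.** Section 3.3 has two blocks of criteria. The pertussis block gives positivity as "Antibody titer is $\geq 0.1$ IU/mL". Its seroconversion rule starts from "Antibody concentration is $< 0.1$ IU/mL before immunization" and requires the child to reach that value afterwards; a child already at or above it needs at least a 4-fold rise. The diphtheria and tetanus block has the same structure with a different number: positivity is "Antibody titer is $\geq 20$ IU/mL" and seroconversion starts from "Antibody concentration is $< 20$ IU/mL before immunization".

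Supplementary Table 1, bound in front of the protocol, reports seroconversion by "subgroups that were positive or negative for antibodies at baseline". It splits anti-PT and anti-FHA at 20 IU/ml, and anti-DT and anti-TT at 0.1 IU/ml.

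Section 1.1 states: "The primary outcomes of the study were the seroconversion rates and seropositive rates of anti-pertussis antibodies in the co-purified DTaP group". It adds the comparison of diphtheria and tetanus seroconversion and seropositive rates between the arms. Hypothesis 1 in the synopsis is that the pertussis seroconversion rate "is not less than 70" percent. Hypothesis 2 is that the diphtheria and tetanus seroconversion rates do not differ between the vaccines.

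**The concern.** The table's title says that its strata are positive and negative children, so its dividing values are positivity cut-offs and not arbitrary subgroup limits. They are the two numbers of Section 3.3, in the same unit, attached to the opposite antigens. Both sets cannot define the same endpoints.

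The cut-off does two jobs. It decides who is seropositive, and it decides whether a child is judged on crossing a threshold or on a 4-fold rise. Every primary outcome is a rate built on one or both of these decisions. A statistician who programs Section 3.3 as printed could therefore classify children differently from one who follows the table, for all four antigens.

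**Working it through.** **1. The two sources side by side**

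| Antigen | Section 3.3 | Supplementary Table 1 |
|---|---|---|
| anti-PT | 0.1 IU/mL (as pertussis; PT not named) | 20 IU/ml |
| anti-FHA | 0.1 IU/mL (as pertussis; FHA not named) | 20 IU/ml |
| anti-DT | 20 IU/mL | 0.1 IU/ml |
| anti-TT | 20 IU/mL | 0.1 IU/ml |

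The ratio is 20/0.1 = 200 for each antigen, upward for two and downward for two.

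**2. The table's own figures.** All 16 percentages reproduce, for example 179/213 = 84.04%, 143/149 = 95.97%, 207/214 = 96.73% and 174/203 = 85.71%. Summed over strata:

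- PT, DTaP arm: (11 + 179)/234 = 190/234 = 81.20%
- FHA, DTaP arm: (31 + 143)/234 = 174/234 = 74.36%
- Diphtheria: 234/234 and 224/224, both 100%
- Tetanus: DTaP (207 + 20)/234 = 227/234 = 97.01%; DT (174 + 21)/224 = 195/224 = 87.05%

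This confirms the arithmetic. It does not show which cut-off produced the numerators.

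**3. What the cut-off does.** For cut-off c, a child is positive if the value is ≥ c. A child seroconverts if pre < c and post ≥ c, or if pre ≥ c and post ≥ 4 × pre. With assumed pre and post values in IU/mL:

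| Antigen, pre to post | Section 3.3 as printed | Table cut-off |
|---|---|---|
| Pertussis, 15 to 25 | not seroconverted | seroconverted |
| Pertussis, 1 to 4 | seroconverted | not seroconverted |
| Pertussis, 5 to 60 | seroconverted | seroconverted |
| Diphtheria/tetanus, 0.5 to 5 | negative, not seroconverted | positive, seroconverted |
| Diphtheria/tetanus, 8 to 25 | seroconverted | not seroconverted |

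Some children change status, in either direction, and some do not.

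**4. Direction, if Section 3.3 is programmed as printed.** Seropositivity is monotone in the cut-off. Lowering the pertussis value to 0.1 can only raise or preserve it; raising the diphtheria and tetanus value to 20 can only lower or preserve it.

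For seroconversion, assume that the table's rates use its stratum cut-offs. Diphtheria is at 100% in both arms and can only fall or stay the same. PT, FHA and tetanus can move either way.

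**5. Who is affected, and the room to move (same assumption).** A child with a pertussis baseline of at least 20 is also above 0.1 and is judged on a 4-fold rise under both rules. The 11/21 (PT) and 31/85 (FHA) therefore do not change. The children at issue have baseline below 20: 213/234 = 91.0% for PT and 149/234 = 63.7% for FHA. Those with baseline at or above 0.1 move to the 4-fold limb.

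- Gains can come only from current non-converters with baseline below 20: at most 213 − 179 = 34 for PT and 149 − 143 = 6 for FHA.
- Losses require post ≥ 20 but post < 4 × pre, hence a baseline above 20/4 = 5 and below 20. The documents do not say how many children lie there.
- For tetanus, gains are limited to 214 − 207 = 7 children in the DTaP arm and 203 − 174 = 29 in the DT arm. Losses are again unknown.

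**6. Sensitivity of the 70% target.** For FHA, 0.70 × 234 = 163.8. A net loss of 174 − 163 = 11 children would give 163/234 = 69.66%, below the target. This shows how small a shift would matter, not that it would occur.

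**The case against.** The strongest reply is that the protocol does not contradict itself here. The conflict is with a results table, and the available text cites no assay source for either set of values; Section 3.3 says only that an ELISA was used. The table also does not restate the seroconversion rule. A reader might infer that each value in Section 3.3 is proved wrong by a factor of 200. The documents do not support that. They show two sources that differ by that factor, and a consistent four-antigen exchange that makes a swap in Section 3.3 likely. This part of the reply stands, and it is why confirmation must come before correction.

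A reader might also infer that every reported rate is wrong or would change. That does not follow. The table's strata already use the exchanged values; if its rates do too, correcting Section 3.3 changes none of them. Even under the printed rule, a change in any given numerator cannot be shown without individual titres.

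Finally, it is tempting to set seroconversion in baseline positives (52% for PT, 36% for FHA) against baseline negatives (84%, 96%) and read the gap as the size of the error. It is not. The baseline positives are unaffected, and the 4-fold rate among children with lower baselines is not given.

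None of this reconciles the two sources. Either the written definition is wrong, or the table departs from it without explanation; the CONSORT checklist marks changes to methods and to outcomes as not applicable.

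**Conclusion.** The point holds as an unreconciled definition of the primary endpoints, and it needs correcting. The cut-offs differ 200-fold for each antigen, and all primary outcomes and both hypotheses depend on them. Harm arises only if Section 3.3 is programmed as printed. Its direction is then bounded for seropositivity and for diphtheria seroconversion, and open for PT, FHA and tetanus seroconversion. The size cannot be stated without titres. GMC and GMI use no cut-off and are unaffected.

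Two assumptions carry weight: that the table's seroconversion rates use its stratum cut-offs, and that the table rather than Section 3.3 shows the intended values. The second is a strong inference, not a demonstrated fact.

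**What to change.** In this order:

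1. Confirm each cut-off and its unit against the assay documentation.
2. Subject to that, correct the two blocks of Section 3.3 together, in both the positivity and the seroconversion definitions, so that they match Supplementary Table 1: 20 IU/mL for anti-PT and anti-FHA, 0.1 IU/mL for anti-diphtheria and anti-tetanus. Name PT and FHA explicitly; this adds a specification, because Section 3.3 speaks only of pertussis.
3. State which cut-offs produced the reported seroconversion and seropositive rates.

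The cost is one wording correction and one statement, with no new data. Rates would need recalculating from existing titres only if the confirmed cut-offs differ from those actually used.

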#### **Immunogenicity assessment criteria for diphtheria vaccine or tetanus vaccine:**

Positive: Antibody titer is  $\geq 20$  IU/mL.

Seroconversion: Antibody concentration is  $< 20$  IU/mL before immunization and  $\geq 20$  IU/mL after immunization; or antibody concentration is  $\geq 20$  IU/mL before immunization and is increased  $\geq 4$ -fold after immunization.

Antibody level: Geometric mean concentrations (GMCs) of serum antibody before and after pertussis vaccine immunization as well geometric mean increase (GMI) in serum antibody

after immunization.

### 3.4 Safety Data Collection

Subjects are observed for 30 min after immunization. Diary cards are distributed after immunization and the subjects must record all solicited and unsolicited adverse events (AEs) observed from D0 to D28 post-immunization in the diary cards every day. Adverse events following immunization (AEFI) will be collected by the investigator using the AEFI monitoring system at 6 months after full immunization. Serious adverse events (SAEs) will also be passively collected at 6 months after full immunization.

#### Solicited AEs:

All solicited AEs observed within 7 d of immunization are assumed by default to be related to the vaccine. The relationship between all unsolicited AEs/SAEs and the vaccines will be determined by the investigator.

✓ Local reactions

Pain, induration, swelling, rash, redness, and pruritus.

Systemic reactions

Fever, fatigue/weakness, decreased appetite, nausea, vomiting, diarrhea, allergy, myalgia, and arthralgia.

### 3.5 Adverse Event Grading Criteria

Post-immunization systemic and local reactions are assessed in accordance with the Guidelines for Classification of Adverse Events in Clinical Trials of Preventive Vaccines (2019 edition) by National Medical Products Administration.

**Table 1. Local reaction grading scale**

| Symptom/Sign                   | Grade 1                                                            | Grade 2                                                  | Grade 3                                                                                                                                     | Grade 4                                                         |
|--------------------------------|--------------------------------------------------------------------|----------------------------------------------------------|---------------------------------------------------------------------------------------------------------------------------------------------|-----------------------------------------------------------------|
| Pain                    | Does not affect or slightly affects activities of the limbs | Affects activities of the limbs                          | Affects activities of daily life                                                                                                            | Loss of self-care abilities or hospitalization           |
| Induration and swelling | Diameter of <2.5 cm                                                | Diameter of ≥2.5cm or area of <50 cm  | area of ≥50 cm  or ulcers or secondary infections or phlebitis or aseptic abscess or wound drainage | Abscess, exfoliative dermatitis, dermal or deep tissue necrosis |

|                         |                                                                                      |                                                                                  |                                                                                                                                                   |                                                                 |
|-------------------------|--------------------------------------------------------------------------------------|----------------------------------------------------------------------------------|---------------------------------------------------------------------------------------------------------------------------------------------------|-----------------------------------------------------------------|
| Rash and redness | Diameter of <2.5 cm                                                                  | Diameter of $\geq 2.5$ cm or area of <50 cm                   | area of $\geq 50$ cm  or ulcers or secondary infections or phlebitis or aseptic abscess or wound drainage | Abscess, exfoliative dermatitis, dermal or deep tissue necrosis |
| Pruritus         | Pruritus at the injection site that resolves within 48 on its own or after treatment | Pruritus at the injection site that does not resolve within 48 h after treatment | Affects activities of daily life                                                                                                                  | NA                                                              |

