**Table 4. Systemic reaction grading scale**

| Symptom/Sign                               | Grade 1                                                                                                      | Grade 2                                                                                      | Grade 3                                                                                                   | Grade 4                                                                                       |
|--------------------------------------------|--------------------------------------------------------------------------------------------------------------|----------------------------------------------------------------------------------------------|-----------------------------------------------------------------------------------------------------------|-----------------------------------------------------------------------------------------------|
| Fever * [axillary temperature (°C)] | 37.3 to <38.0                                                                                                | 38.0 to <38.5                                                                                | 38.5 to <39.5                                                                                             | $\geq 39.5$ for 3 d                                                                           |
| fatigue/weakness                    | Does not affect activities of daily life                                                                     | Slightly affects activities of daily life                                                    | Severe myalgia, severely affects activities of daily life                                                 | Emergency care or hospitalization                                                             |
| decreased appetite                  | Decreased appetite, but not reduced food intake                                                              | Appetite decreased and food intake decreased, but body weight did not decrease significantly | Decreased appetite and weight                                                                             | Interventions are needed (such as gastric tube feeding, parenteral nutrition)                 |

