| Nausea                              | Transient (<24 h) or intermittent and normal food intake                                              | Persistent nausea leading to decreased food intake (24–48 h)                                 | Persistent nausea leading to nearly no food intake (>48 h) or requires intravenous rehydration     | Life-threatening (such as hypotension shock)                                                  |
| Vomiting                            | 1–2 times/24 h and does not affect activity                                                           | 3–5 times/24 h or limited activities                                                  | >6 times/24 h or requires intravenous rehydration                                                  | Requires hospitalization or other routes of nutrient delivery due to hypotension shock |
| Diarrhea                            | Mild or transient, 3–4 times/d, abnormal stool property, or mild diarrhea that persists for less than 1 week | Moderate or persistent, 5–7 times/d, abnormal stool property, or diarrhea that lasts >1 week | >7 times/d, abnormal stool property, or hemorrhagic diarrhea, orthostatic hypotension, electrolyte | Hypotension shock, requires hospitalized treatment                                            |

|                                     |                                                       |                                                                                                          |                                                                                          |                                                                                      |
|-------------------------------------|-------------------------------------------------------|----------------------------------------------------------------------------------------------------------|------------------------------------------------------------------------------------------|--------------------------------------------------------------------------------------|

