|                                     |                                                       |                                                                                                          | imbalance,
requires >2 L
intravenous infusion                                      |                                                                                      |
| Acute allergic reactions     | Local urticaria (blister), does not require treatment | Local urticaria, requires treatment or mild angioedema, does not require treatment                | Extensive urticaria or angioedema requiring treatment or mild bronchospasm | Anaphylactic shock or life-threatening bronchospasm or laryngeal edema |
| Myalgia (non-injection site) | Does not affect activities of daily life              | Slightly affects activities of daily life                                                                | Severe myalgia, severely affects activities of daily life                                | Emergency care or hospitalization                                                    |
| Arthralgia                   | Mild pain, does not affect function                   | Moderate pain; requires analgesics and/ or pain affects function but not activities of daily life | Severe pain; requires analgesics and/ or pain affects activities of daily life    | Disabling pain                                                                       |

Clinical abnormalities not mentioned in the above table can be graded according to the following adverse reaction criteria:

| Grade 1                                                           | Grade 2                                                                                                              | Grade 3                                                                                                            | Grade 4                                                                                                                               | Grade 5 |

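### Grade 2 for size-graded local reactions is joined by *or* and so covers every lesion size, overlapping Grades 1 and 3; three systemic rows also need reconciling

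*Combined protocol and SAP*

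**What the plan says.** Section 3.5 says that local and systemic reactions are assessed under a 2019 national guideline for grading adverse events in preventive vaccine trials. It then prints its own tables.

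In Table 1, induration and swelling share a row, and so do rash and redness. In both rows Grade 1 is "Diameter of <2.5 cm". Grade 2 is "Diameter of ≥2.5cm or area of <50 cm" squared for induration and swelling, and "Diameter of $\geq 2.5$ cm or area of <50 cm" squared for rash and redness. Grade 3 by size is an area of at least 50 cm²; listed complications also give Grade 3.

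In Table 4:

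- **Fever** is Grade 3 from 38.5 to below 39.5 °C, and Grade 4 at 39.5 °C or above for 3 days. The row label carries an asterisk whose footnote is not in the supplied text.
- **Vomiting** is Grade 2 at "3–5 times/24 h or limited activities" and Grade 3 at ">6 times/24 h or requires intravenous rehydration".
- **Fatigue/weakness** at Grade 3 reads "Severe myalgia, severely affects activities of daily life".

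A generic scale follows Table 4, introduced by "Clinical abnormalities not mentioned in the above table can be graded according to the following adverse reaction criteria". The supplied text has no rule for an event that meets two grades.

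**The concern.** A severity scale should give each observation one grade. Joined by *or*, the Grade 2 size cell is met if either half is true, and together the halves take in everything: small lesions satisfy the area half and large ones the diameter half. The person grading then has to choose between two grades that both fit the text.

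Safety is part of the stated study objective, and all four signs in these rows are solicited local reactions (section 3.4). The design is open-label, so a choice left to discretion could be made differently in the two arms. What is at stake is the split between Grades 1 and 2 and between Grades 2 and 3 for these signs and, through the fever row, the grading of the highest short fevers.

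**Working it through.** The plan gives no figure to reproduce here. The check applies the printed cells as logical rules.

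**Inputs, from Table 1.** With *d* the largest diameter in cm and *A* the area in cm²:

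- Grade 1: *d* < 2.5
- Grade 2: *d* ≥ 2.5 or *A* < 50
- Grade 3 by size: *A* ≥ 50

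**Step 1, small lesions.** For a circle, *A* = π*d*²/4. At *d* = 2.5, *A* = π × 6.25 / 4 = 4.91 cm². If area is taken as length × width, the bound is 2.5 × 2.5 = 6.25 cm². Both are far below 50, so every Grade 1 lesion also satisfies the area half of Grade 2.

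**Step 2, large lesions.** A circle of 50 cm² has *d* = 2√(50/π) = 7.98 cm. By length × width, the longer side is at least √50 = 7.07 cm. Both exceed 2.5, so every lesion that is Grade 3 by size also satisfies the diameter half of Grade 2.

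**Step 3, the whole range.** For circular lesions from 0.01 to 15 cm in steps of 0.01 cm:

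| Diameter (cm) | Size grades met with *or* | Size grades met with *and* |
|---|---|---|
| 0.01 to 2.49 | 1 and 2 | 1 |
| 2.50 to 7.97 | 2 | 2 |
| 7.98 to 15 | 2 and 3 | 3 |

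**Step 4, would a tie-break do?** If the highest grade met were taken under the printed *or*, every Grade 1 lesion would become Grade 2 and Grade 1 by size would never be used. If the lowest were taken, every lesion that is Grade 3 by size would become Grade 2. Neither rule restores three size bands. Changing the connective does.

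**Step 5, systemic rows in Table 4.**

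- *Fever.* Reading the duration as lasting 3 days, 39.4 °C is Grade 3 at any duration. By contrast, 39.5, 40 or 41 °C for 1 or 2 days meets no printed grade, and for 3 days meets Grade 4.
- *Vomiting.* By count, 5 episodes in 24 h is Grade 2, 7 is Grade 3, and 6 is neither.
- *Fatigue.* The Grade 3 cell is identical to the Grade 3 cell for myalgia, which is a separate solicited event. The other three fatigue cells match the myalgia row as well, which points to a copying slip.

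The generic scale does not close the fever or vomiting gap, because it is reserved for abnormalities that the table does not mention.

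**The case against.** The best reply is that the intended size bands are easy to recover. The cells form an ordered scale, and if a small area alone gave Grade 2, Grade 1 could never stand by itself. A sensible grader would read Grade 2 as at least 2.5 cm and short of Grade 3. Section 3.5 also defers to a national guideline that graders may have had to hand, and the printed table may be a loose rendering of it. That is plausible, and nothing in the documents shows that graders disagreed. But the guideline is not reproduced, the supplied text does not say which prevails, and the same *or* stands in both size rows, so a text-extraction error is unlikely. A rule that needs repair by its reader should be repaired on the page.

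Several limits stand in full:

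- A reader might infer that every local reaction fits two grades. Pain and pruritus are not graded by size, and lesions between 2.5 and about 8.0 cm meet Grade 2 only.
- A reader might infer that every short fever of 39.5 °C or more is ungradable. The missing footnote to the fever row could deal with this, so the point is conditional.
- Six vomits can still be graded on the non-count criteria: limited activity, intravenous rehydration, or hospital care for hypotensive shock. The gap is one count value.
- Fatigue Grade 3 still carries a functional criterion that completes the sequence from Grades 1 and 2.
- Both hypotheses, the listed primary and secondary outcomes and the sample size concern immunogenicity. The supplied text contains no grade-based hypothesis, threshold or stopping rule.

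**Conclusion.** The concern holds for the two size-graded rows of Table 1. As printed, every lesion that is Grade 1 by size and every lesion that is Grade 3 by size also meets Grade 2, whether area is computed as a circle or as length × width. The written rule therefore does not fix the severity tabulation of induration, swelling, rash and redness. The fever, vomiting and fatigue cells are lesser inconsistencies of the same kind, and the fever one depends on the unseen footnote.

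It would be tempting to conclude that adverse events were lost or that the comparison between arms is biased. The documents support neither. A reaction with an uncertain grade still counts as an adverse event, so overall incidence is unaffected, and differential grading is a possibility under an open label rather than something shown. The number of affected children cannot be derived, because no lesion sizes, temperatures or vomiting counts are given. The immunogenicity endpoints and the sample size are untouched.

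**What to change.** 1. Check the two Grade 2 size cells in Table 1 against the cited 2019 guideline and change *or* to *and*, so that Grade 2 requires a diameter of at least 2.5 cm and an area below 50 cm². The size bands then no longer overlap.
2. Do not add a rule to record the highest grade met without that change, since it would abolish Grade 1 by size. Once the change is made, the rule is not needed to separate the size bands.
3. Reconcile the fever, vomiting and fatigue rows of Table 4 with the same guideline so that each value maps to one grade, and print the footnote to the fever row. What those cells should say is for the sponsor to settle from the guideline.
4. Supplementary Table 1 shows that results already exist, so state which grading rule was applied. Where diameters, temperatures and counts were recorded, derive the grades from them under the corrected table, by the same rule in both arms.

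The cost is table wording, diary and case report form coding, and a re-derivation from data already held. No new procedures or visits are needed.
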